## Abstract

**Background:**

Haemorrhage remains a leading cause of morbidity and mortality in trauma patients. Fibrinogen is an essential endogenous component of haemostasis and the plasma level is associated with bleeding, transfusion and outcome. Fibrinogen concentrate is widely used to correct acquired hypofibrinogenaemia, recommended by several international guidelines for the treatment of trauma patients, but evidence is lacking regarding the treatment safety and efficacy.

We aim to assess the efficacy and safety of an immediate pre-emptive first-line treatment with fibrinogen concentrate in patients with trauma haemorrhage in need of haemostatic resuscitation.

**Methods/Design:**

This is a single-centre, randomized (1:1, active:placebo), placebo-controlled, double-blinded, investigator-initiated phase II trial. The trial population consists of 40 adult patients (>18 years) with traumatic, critical bleeding admitted to the Level 1 Trauma Centre at Rigshospitalet in Copenhagen, with immediate need for blood transfusion on arrival and an expected need for haemostatic resuscitation with multiple transfusions during the initial resuscitation. Patients will receive either pre-emptive administration of a bolus dose of 60–70 mg/kg fibrinogen concentrate (Riastap®) or placebo 0.9 % saline in equal volume to active treatment, both given as intravenous infusion blinded for the person administering the infusion.

The primary end point is the change in thrombelastograph (TEG®) functional fibrinogen maximum amplitude in millimetres at 15 min after the intervention. The follow-up period on safety events and mortality will be until day 30.

To detect a difference in the change from baseline to the 15-minute post-randomization measurement of 6–8 mm in TEG® functional fibrinogen maximum amplitude with a power of 0.90 and alpha of 0.05, we require 19 patients in each group. We have chosen to include 40 patients, 20 evaluable patients in each randomization group in case of attrition, in the present trial.

**Discussion:**

Patients considered to be included in the trial will temporarily have a compromised consciousness because of the acute, critical bleeding related to trauma, so scientific guardians will co-sign the informed consent form. Next of kin and the patients’ general practitioner or the patients will co-sign as soon as possible.

This trial will test whether immediate pre-emptive fibrinogen concentrate administered to adult trauma patients as first-line treatment of trauma haemorrhage will increase the clot strength as evaluated by thrombelastography, transfusion requirements and survival in patients receiving haemostatic resuscitation according to current standard of care.

**Trial registration:**

EudraCT no. 2014-003978-16 (22/1 2015); ClinicalTrials.gov: NCT02344069. Registered on 14 January 2015. Trial protocol version 4.2 (23-12-2014).

## Background

Haemorrhage remains a leading cause of morbidity and mortality in trauma patients [1]. Fibrinogen is an essential endogenous component of haemostasis [2] and the plasma level is associated to bleeding, transfusion and outcome [3]. Fibrinogen concentrate is widely used to correct acquired hypofibrinogenaemia, recommended by several guidelines [4, 5], but evidence is lacking regarding the treatment efficacy [6, 7].

Several trauma resuscitation strategies are currently being employed and investigated internationally [8]. The concept of haemostatic resuscitation is widely used in which early pre-emptive balanced transfusion therapy with red blood cells (RBC): fresh frozen plasma (FFP): platelets (PLT) are driven according to fixed ratios aiming at 1:1:1. The best evidence for this concept comes from Holcomb and colleagues, showing a beneficial effect of high ratios on haemostasis and short-term mortality due to exsanguination [9]. The Copenhagen Concept, Haemostatic Control Resuscitation (HCR), implemented in 2004, is a further adaptation of haemostatic resuscitation comprising of balanced transfusion therapy with transfusion packages equal to a ratio 1:1:1 in the early phase of massive bleeding, and then adjusting the therapy according to viscoelastic haemostatic assay-based algorithms allowing for goal-directed treatment of coagulopathy [1, 10]. The standard of trauma care in our facility is based on Advanced Trauma Life Support (ATLS) with strong focus on haemorrhage control, and early whole-body computed tomography (CT) if the patient is stable. Tranexamic acid is standard of both pre- and intrahospital care in Denmark according to the CRASH-2 trial [11]. HCR is associated with improved survival in observational studies, but still, in most resuscitation concepts, including HCR, a low level of fibrinogen is associated with coagulopathy, low clot strength and poor outcome [1, 3].

Fibrinogen is a key element not only in secondary haemostasis, where it is cleaved by thrombin to form fibrin, but also in primary haemostasis by facilitating platelet aggregation and adhesion [12]. Fibrinogen levels average 2–4 g/l in healthy individuals and have been shown to be the element of the coagulation system that first reaches low levels during haemorrhage, at least if volume replacement is based on RBC and fluids alone [13], and in conditions with hyperfibrinolysis [14]. The “critical level” at which acquired fibrinogen deficiency causes a decrease in haemostatic competence is, however, debatable. Studies in patients with congenital fibrinogen deficiencies indicate that only levels below 1 g/l cause an increase in bleeding during surgery [6], and this level has generally been adopted as a target for substitution in bleeding patients with acquired deficiencies also [6, 15]. A level as high as 1.5–2 g/l is now being suggested as the target for substitution since decreased levels have been associated with worse outcomes in bleeding patients [3–5, 16, 17]. In regard to the use of fibrinogen concentrate in bleeding trauma patients, no data from prospective randomized controlled trials (RCT) have been published. However, there are another ongoing study (NCT01475344), and the FiiRST study (NCT02203968) that is completed, but with no results published yet. The CRYOSTAT pilot trial showed that cryoprecipitate supplementation containing fibrinogen in trauma is feasible and that a definitive trial is warranted to see the effect on safety, transfusions, morbidity and mortality [18]. However, cryoprecipitate is more than fibrinogen substitution since all coagulation factors are in there and it may not be comparable to fibrinogen concentrate primarily containing fibrinogen [19]. Outside trauma, the evidence for use of fibrinogen is also very scarce and most studies are with high risk of bias [15]. Moreover, in the latest RCT on severe postpartum haemorrhage no evidence to support the preemptive use of 2 g fibrinogen concentrate was found, however no concern related to safety and thromboembolic complications in particular appeared [20].

The objective of this trial is to assess the efficacy and safety of an immediate pre-emptive first-line treatment with fibrinogen concentrate in patients with trauma haemorrhage in need of haemostatic resuscitation. We hypothesize that immediate pre-emptive fibrinogen concentrate administered to adult trauma patients as first-line treatment of traumatic haemorrhage will increase the clot strength as evaluated by thrombelastography (TEG®).

## Methods/design

This is a single-centre randomized, double-blinded, controlled, investigator-initiated, pilot phase II trial of 40 haemorrhaging trauma patients admitted to the Level 1 Trauma Centre in Copenhagen, Denmark randomized to administration of fibrinogen concentrate (Riastap®, CSL Behring Scandinavia, Danderyd, Sweden), as compared to placebo (saline), as immediate, pre-emptive first-line treatment of trauma haemorrhage, when haemostatic resuscitation is needed.

### Patients

The study will include 40 adult (≥18 years) trauma patients received directly from the scene of the accident, where an order of at least one blood component transfusion within the first hour of arrival is initiated, and the patient is predicted to need transfusion package therapy during the first 2 hours (activated massive transfusion protocol) [10]. Detailed inclusion and exclusion criteria are listed in Table 1. A written informed consent will be obtained from patients or scientific guardians (independent physicians and/or next of kin).

**Table 1 Tab1:** Selection criteria

Inclusion criteria
• Trauma patient received directly from the scene of the accident AND • Age ≥18 years AND • Initiated order of transfusion of at least one blood component within the first hour of arrival AND • Predicted to need transfusion package therapy during the initial resuscitation (first 2 hours) AND • Consent obtainable from patient or scientific guardians (independent physicians and/or next of kin)
Exclusion criteria
Patients are not eligible for inclusion in this trial if they fulfill one or more of the following criteria: • Duration of >2 hours from time of accident to arrival at trauma centre OR • Known anticoagulant treatment (vitamin K antagonist, dabigatran, rivaroxiban, apixaban) OR • Severe isolated traumatic brain injury OR • Moribund patient with devastating injuries and expected to die within 1 hour of admission OR • Withdrawal from active therapy OR • Previously, within 30 days, included in a randomized trial, if known at the time of enrolment OR • Known body weight <55 kg OR • Any blood product prior to inclusion

### Randomization

The randomization is done in blocks of six, and the randomization sequence and envelopes are generated and validated by two persons that are otherwise not involved in the trial. Randomization was performed using Microsoft Excel software (Microsoft Corp., Redmond, WA, USA). Treatments (fibrinogen concentrate - Riastap® or placebo/saline) were arranged in two groups of 20 patients in a single column in a systematic order. Each block of six patients included three fibrinogen concentrate - Riastap® and three placebo/saline patients. A second column was created for random numbers and the treatments column was then sorted by these random numbers [21].

Two identical sets of envelopes are generated - one set for randomization of patients at the Trauma Centre, and an “emergency” set for code breaking if necessary. Written and signed documentation for the double-controlled generation of randomization envelopes is kept at the Blood Bank. The randomization sequence is kept secret for the investigators by use of successively numbered, sealed, and opaque envelopes. Each patient is given a unique randomization number.

Emergency department nurses in the Trauma Centre, not involved in treatment of the specific patient, will perform 24-hour on-site randomization by envelope-opening to allow for immediate allocation to either receiving fibrinogen concentrate (intervention) or saline (placebo). A written instruction for the randomization procedure is kept with the envelopes.

A randomization list is held by the sponsor, which will be available to the investigator after the completion of the trial. Emergency code-breaking envelopes are available in the Blood Bank where they can be opened if decided by the sponsor.

### Interventions

The treating physician must have evaluated the patient’s eligibility and approved the patient’s enrolment in the trial prior to administration of the trial drug/placebo. All patients will be treated according to normal standard of care for haemorrhaging trauma patients.

The trial/placebo drug is administered as an intravenous bolus dose as early as possible during the initial resuscitation (Fig. 1). During the infusion the patient will be observed especially with regard to potential signs of thrombotic and allergic complications.

**Fig. 1 Fig1:**
[figure not shown]
Trial flow diagram

#### Experimental arm

The active treatment (n = 20 patients) consists of intravenous injection of fibrinogen concentrate (Riastap®) of 60–70 mg/kg (dose of 4 g for patients with body weight 55–69 kg, 5 g for 70–85 kg or 6 g for >85 kg) as a bolus dose when haemostatic resuscitation is deemed necessary by the clinician. Fibrinogen is administered as an immediate single intravenous injection, according to Solomon et al. [22, 23]. The aim is to give the intervention <1 hour of arrival, and the intervention should, when possible, be given prior to blood products.

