### Missing data

If for any of the analyses mentioned above there are less than 95 % of the observations which are complete, we will employ multiple imputation techniques for that analysis [24]. The multiple imputation approach will be based on chained equations. If more than 95 % of the observations are complete, we will only employ complete case analysis.

The power calculation is based on local data finding of a TEG® FF MA mean 13.6 mm (SD ± 5.6) on arrival in trauma patients not surviving for 30 days. Administering 60–70 mg/kg fibrinogen concentrate will result in an approximate increase of 6–8 mm in TEG FF MA according to Tanaka and colleagues, which corresponds to increasing the fibrinogen level with approximately 1 g/l and to a level of above 2.3 g/l [25]. To detect the above difference with a power of 0.90 (1-β) and alpha of 0.05 requires n = 19 patients in each group. We have chosen to include 40 patients, 20 evaluable patients in each randomization group in case of attrition, in the present trial. Patients who drop out or are withdrawn for any reason before hour 24 will be replaced.

No interim analysis is planned. The actual statistical power will be a bit higher as the primary end point is a change value and we adjust the analysis for baseline values. However, the exact size of this additional power cannot be readily assessed as we do not have reliable information about the intra-person correlation of TEG® FF MA.

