## Discussion

A low level of fibrinogen is associated with coagulopathy, low clot strength and poor outcome, and fibrinogen concentrate is currently being used at various facilities at the discretion of the physician on a case-by-case basis, often goal-directed according to viscoelastic haemostatic assays such as thrombelastography (TEG®) or thrombelastometry (ROTEM®)[1, 3]. The Pilot Randomized trial of Fibrinogen in Trauma Haemorrhage (PRooF-iTH) is the first randomized controlled trial of fibrinogen in trauma. Furthermore, the first trial to address whether first-line, pre-emptive fibrinogen concentrate treatment will increase the clot strength, and influence transfusion requirements and survival in adult trauma patients in need of haemostatic resuscitation. Included patients will have critical or massive bleeding in need of activation of our massive transfusion protocol.

When administering a pro-haemostatic drug such as fibrinogen concentrate, there is a possible risk of thromboembolic events. In seven randomized controlled trials on the use of fibrinogen concentrate as a pro-haemostatic drug, six of these were in cardiac surgery carrying an inevitable increased thromboembolic risk, and only one trial has reported two cases of thromboembolic events [26]. However, in a 22-year pharmaco-surveillance programme with more than 1,000,000 g of fibrinogen concentrate administered, only nine cases of thrombosis possibly related to the treatment have been reported [27]. Furthermore, in a recent randomized controlled trial using 2 g fibrinogen substitution or placebo in 249 patients with severe postpartum haemorrhage done by our group, we saw no thromboembolic events and no serious adverse events or reactions [28]. In conclusion, the risk of thromboembolic events seems negligible when fibrinogen is used in a relevant population, with potential important benefits.

The dose of fibrinogen concentrate in the present trial is 60–70 mg/kg and was chosen based on the reported findings of low concentration of fibrinogen in actively haemorrhaging trauma patients [29, 30] and it is estimated that the chosen dose will increase the functional fibrinogen maximal amplitude by 6–8 mm resulting in significantly higher overall clot strength [25]. Importantly, no clinical or preclinical data indicate that administration of fibrinogen concentrate to patients having a normal fibrinogen leads to a hypercoagulable or pro-thrombotic state [20].

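### The gram-by-weight bands do not give the stated 60–70 mg/kg at every eligible weight, chiefly above 100 kg, so the two dose statements need reconciling

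*Protocol article*

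**What the plan says.** The dose appears in four places in the protocol article.

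- Abstract, Methods/Design: "a bolus dose of 60–70 mg/kg fibrinogen concentrate".
- Interventions, Experimental arm: "intravenous injection of fibrinogen concentrate (Riastap®) of 60–70 mg/kg", followed in brackets by the amounts to be given, "dose of 4 g for patients with body weight 55–69 kg" and "5 g for 70–85 kg or 6 g for >85 kg".
- Missing data, in the paragraph on the power calculation: "Administering 60–70 mg/kg fibrinogen concentrate will result in an approximate increase of 6–8 mm in TEG FF MA".
- Discussion: "The dose of fibrinogen concentrate in the present trial is 60–70 mg/kg", again linked to the 6–8 mm rise.

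Eligibility by weight is in Table 1, which excludes "Known body weight <55 kg" and sets no upper limit. Table 3 schedules weight and drug administration at baseline.

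**The concern.** A mg/kg range and a set of fixed gram amounts can both describe the dose only if grams divided by weight stays inside the range for every weight the trial admits. The top band is open-ended and eligibility has no upper weight limit, so this cannot be taken for granted and needs checking.

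What is at stake is how the trial describes its own intervention. The primary end point is a laboratory response to this dose 15 minutes after it is given. The planning effect of 6–8 mm and the dose rationale are both stated for 60–70 mg/kg. If some active patients receive less, a report that the active arm received 60–70 mg/kg would be untrue for them, and the observed rise would be set against a dose they did not get.

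**Working it through.** **Inputs.** Bands from the Experimental arm section: 4 g for 55–69 kg, 5 g for 70–85 kg, 6 g above 85 kg. Stated range: 60–70 mg/kg. Eligible weights from Table 1: 55 kg upward, no ceiling. The bands are written in whole kilograms and are checked that way.

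**The plan's own figure.** The stated 19 per group is reproduced with 6 mm, SD 5.6 mm, 90% power and alpha 0.05, taken as two-sided (the article does not state sidedness):

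n = 2 × (1.960 + 1.282)² × 5.6² / 6² = 2 × 10.51 × 0.871 = 18.3, rounded up to 19.

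The calculation therefore uses the low end of the 6–8 mm range. An exact t-test calculation gives 20, which is the number planned per group.

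**Delivered dose.** mg/kg = grams × 1000 / weight in kg.

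| Weight (kg) | Grams | mg/kg | Against 60–70 |
|---|---|---|---|
| 55 | 4 | 72.7 | 2.7 above |
| 57 | 4 | 70.2 | 0.2 above |
| 67 | 4 | 59.7 | 0.3 below |
| 69 | 4 | 58.0 | 2.0 below |
| 70 | 5 | 71.4 | 1.4 above |
| 71 | 5 | 70.4 | 0.4 above |
| 84 | 5 | 59.5 | 0.5 below |
| 85 | 5 | 58.8 | 1.2 below |
| 86 | 6 | 69.8 | inside |
| 100 | 6 | 60.0 | inside |
| 110 | 6 | 54.5 | 5.5 below |
| 120 | 6 | 50.0 | 10.0 below |
| 130 | 6 | 46.2 | 13.8 below |

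**Where range and bands agree.** Solving for weight:

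- 4 g: 4000/70 = 57.1 to 4000/60 = 66.7 kg
- 5 g: 5000/70 = 71.4 to 5000/60 = 83.3 kg
- 6 g: 6000/70 = 85.7 to 6000/60 = 100 kg

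In whole kilograms the compliant weights are 58–66 (9), 72–83 (12) and 86–100 (15), which is 36 of the 46 weights from 55 to 100 kg. The remaining ten are 55–57, 67–71 and 84–85 kg. Above 100 kg no weight complies, and the dose keeps falling as weight rises.

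**Does this disturb the sample size?** The article gives neither a weight distribution nor a dose–response slope, so this step rests on assumptions. Take normal weights with mean 75–90 kg and SD 12–18 kg, cut off below 55 kg, and an effect proportional to mg/kg.

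- Mean delivered dose: 61.4 to 64.4 mg/kg, inside the stated range.
- Share of patients below 55 mg/kg (above about 109 kg): 0.2% to 14.8%. In an arm of 20 that is 20 × 0.002 = 0.04 to 20 × 0.148 = 3.0 patients expected.
- Power at 19 per group (normal approximation): 0.92–0.94 if 6 mm belongs to 60 mg/kg, and 0.88–0.91 if 6 mm belongs to 65 mg/kg. With 20 per group the latter becomes 0.89–0.92.

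Power stays close to the planned 0.90 throughout, before the gain from baseline adjustment that the article mentions but does not count.

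**The case against.** The best reply is that there is one dosing rule, not two. The bracketed grams spell out how the nominal range is to be given, and staff working from the bands know what to give at any whole-kilogram weight from 55 kg up. The other sections repeat the range as a summary, so at most the text lacks a qualifier such as approximately.

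Much of this stands. The bands are workable, and misses of up to 2.7 mg/kg between 55 and 100 kg are what whole-gram steps produce. It does not cover weights above 100 kg, where the gap is 10 mg/kg at 120 kg and still growing; rounding does not explain that. The article also gives the range without a qualifier. In the power paragraph, the word approximate applies to the rise in millimetres, not to the dose.

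A second reply is that weight and administration are already recorded, so delivered mg/kg can be derived, and whether to tabulate it may be settled in the full protocol or SAP. That is fair: the absence of such a table from the article is not a fault.

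A reader might also infer that a patient under 55 kg whose weight is unknown at enrolment could enter with no band to apply. The text gives this little support. Table 3 schedules weight at baseline before infusion, and a patient then found to be below 55 kg has a known weight that meets the exclusion.

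**Conclusion.** The contradiction is certain, since it follows by division from the article's own figures. It is limited in extent: small and explicable by rounding at ten whole-kilogram weights up to 100 kg, systematic and unbounded above 100 kg. How many patients this affects cannot be known from the article, and any share depends on an assumed weight distribution.

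Two stronger readings should be resisted. One is that the bands fail to deliver 60–70 mg/kg in general; they deliver it at most weights from 55 to 100 kg. The other is that the trial is underpowered as a result. The stated 19 per group reproduces at the low end of the effect range, the mean dose stays inside 60–70 mg/kg under the weight distributions tried, and the article offers no slope from which a smaller effect could be derived. What is lost is accuracy in the stated exposure, not a demonstrated amount of power. Randomization, the primary analysis and the sample size are untouched.

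**What to change.** Reconcile the mg/kg range in the Abstract, the Experimental arm section, the power paragraph and the Discussion with the weight bands. The stated exposure, and the dose to which the 6–8 mm rise is tied, should then match what is delivered across all eligible weights, including those above 100 kg. Whichever statement the sponsor keeps, the other must be brought into line with it. Which one is right is a clinical decision for the sponsor and is not judged here.

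In the results, summarise delivered mg/kg in the active arm from the baseline weight and administration records, so that readers can see the actual exposure.

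The cost is a wording correction in four places and one descriptive line. No extra patients, measurements or changes to the analysis are needed.

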#### Control arm

Patients in the placebo group (n = 20 patients) will receive 0.9 % saline infusions in equal volume to active treatment and will be treated exactly as active patients. The volume of placebo administered is equal to the volume of active drug administered, again as a bolus dose when haemostatic resuscitation is deemed necessary by the clinician.

The content (Riastap® or placebo) will be provided in opaque syringes and infusion sets (yellow-coloured) to disguise the content of the allocation to the treatment team.

